### 2.1.6 Timing of Analyses

The final analysis of the primary outcome will be performed after the completion of the last visit of the last patient.

### 2.1.7 Sample size

In a pilot trial [19] the experimental group (n=27) improved from  $19.26 \pm 3.92$  to  $10.67 \pm 6.42$  (mean $\pm$ SD) and the control (n=25) from  $20.68 \pm 3.96$  to  $14.92 \pm 7.58$  on the GDS. Thus, assuming correlation of 0.5 between measurements (pre to 6 months post randomization), a standardized difference of about 0.52 ( $\approx 2.83/5.47$ ) was observed between groups. Our multicentre trial should be powerful enough to detect a clinically relevant difference of 2.5 GDS points ( $d=0.4$ ). Thus, the two-sample t-test requires 99 subjects per group to reach 80% power at two-sided significance level 5%. Accounting for up to 20% attrition and stratification, 124 ( $\approx 99/0.8$ ) subjects need to get randomized per group, i.e. 248 subjects in total. Adjusting for baseline in a mixed model for repeated measures (MRM) approach is likely to further increase the statistical power (see below).

## 2.2 Analysis populations

### 2.2.1 Definitions

Full analysis set (FAS)

- The primary (full) analysis set (FAS) is derived from the intention-to-treat principle (all subjects randomized with a valid baseline assessment and at least one valid followup outcome assessment). Per-protocol-set (PPS)
- The per-protocol-set is defined as a subset of the FAS population (all subjects without major protocol violations and at least 9 sessions in one of the therapeutic intervention as scheduled in the trial protocol).

Safety analysis set (SAF)

- All subjects with at least one treatment.

### 2.2.2 Major protocol violations / Withdrawals

Each subject will be informed that participation is voluntary and withdrawal is possible at any time.

Subjects who withdraw or stop treatment prematurely will not be replaced.

Additionally to the withdrawal of subjects, the Investigator can stop the participation of a subject after consideration of the benefit/risk ratio. Other possible reasons for the Investigator to discontinue a subject's trial treatment or participation include:

- Any relevant deterioration in the health of the subject possibly impacting the participation in the trial, including adverse events, severe medical condition, major surgery, laboratory parameters, vital signs or other safety parameters at the discretion of the Investigator
- Regular use with scheduled dosing of benzodiazepines (NB: not PRN) or change of antidepressive pharmacological treatment during 8-week intervention

- Parallel psychiatric or psychotherapeutic interventions (including but not limited to ECT, TMS, tDCS, VNS) during the treatment period
- Technical reasons (e.g. subject moves away)

## 2.4 Analysis variables

### 2.4.1 Demography and baseline characteristics

Demographic variables

- Sex
- Age
- Marital status
- Family status
- Family history
- Housing situation
- Education
- Occupation
- Nationality/ethnicity

Medical variables

- Psychiatric and psychotherapeutic history
- Psychiatric and psychotherapeutic present treatment
- Medication
- Somatic symptoms
- Somatic diseases
- Weight
- Height

- BMI
- Level of physical activity
- Blood measurement
  - o Genetic and epigenetic analyses
  - o Measurement of Amyloid- $\beta$  and Neurofilament light chain (NFL)
  - o miRNA analyses
  - o Metabolomics and Proteomics
  - o PBMC analyses
- Magnetic Resonance Imaging (MRI)
  - o High-resolution structural image
  - o resting-state fMRI
  - o Diffusion Tensor Imaging (DTI)

#### 2.4.2 Primary variable

- Change in Geriatric Depression Scale (GDS) from baseline to end-of-treatment (week 10)

#### 2.4.3 Secondary variables

- Change in Geriatric Depression Scale (GDS) from baseline to end of follow-up (month 6)
- Changes from baseline to end-of-treatment and to end of follow-up in:
  - o Quick Inventory of Depressive Symptomatology (QIDS-C)
  - o Geriatric Anxiety Inventory (GAI)
  - o Patient-Reported Outcome in Major Depressive Disorder (PRO-MDD)
  - o Health Status (SF 36)
  - o Insomnia Severity Index (ISI)
  - o Epworth Sleepiness Scale (ESS)
  - o EM Sleep Behavior Disorder Screening Questionnaire (RBDSQ)
  - o Consortium to Establish a Registry for Alzheimer's Disease neuropsychological battery (CERADplus)
  - o Subtest of the Neuropsychological Assessment Battery (NAB)
- Influences of traumatic experiences, and personality traits on the change in GDS will be assessed at baseline by:
  - o Childhood Trauma Questionnaire (CTQ-SF)
  - o Big Five Inventory-10 (BFI-10)
- Longitudinal Interval Follow-up Evaluation (LIFE)

##### 2.4.3.1 Safety/Tolerability

- Adverse events
- Serious adverse events
- Assessment of suicidality

##### 2.4.3.2 Quality of life

- WHO Quality of Life (WHOQOL-OLD, WHOQOL-BREF)

## 2.5 Handling of missing values and outliers

### 2.5.1 Missing values

Missing values will not be substituted; however, see below section 6.3.

### 2.5.2 Outliers

No outlier analysis will be done.

## 2.6 Statistical analyses / methods

### 2.6.1 Patient / Subject Disposition

The number of patients screened will be determined from local documentation. The frequency of screening failures due to specific inclusion and exclusion criteria will be reported. Multiple selections per patient were possible.

Application of the inclusion and exclusion criteria to all included subjects will be verified. Frequencies will be shown in a subject flow diagram. Number of and reasons for drop-outs will be included.

### 2.6.2 Demography and baseline characteristics

Demographic and baseline characteristics will be summarized descriptively by treatment arm for ITT, PPS, and SAF.

Descriptive statistical analyses include: Number of subjects (n), arithmetic mean, standard deviation (SD), median, first quartile (Q1), third quartile (Q3), minimum (min), maximum (max) for quantitative variables and absolute and relative frequencies for qualitative variables.

### 2.6.3 Primary analysis

The primary objective of this study is to test the hypothesis that a 15-session individually delivered cognitive behavioural therapy (CBT) specific for late life depression (LLD) is of superior efficacy in reducing symptoms of depression in comparison with a supportive unspecific intervention (SUI) of the same quantity in subjects with LLD.

The primary outcome measure „change in GDS from baseline to end-of-treatment (week 10)“ is evaluated by a mixed model for repeated measures (MMRM) with fixed effects baseline, therapist, group, time and the interaction group\*time (ARH1-structured covariance matrix over time) with corresponding marginal means and contrast tests. Data from low recruiting therapists (i.e. < 4 subjects) are pooled by study centre. (In a supplementary analysis all therapists are pooled by centre.) The potential clustering of observations of participants by therapist or centre will be investigated by multilevel modelling. Since mixed models can be expected to yield valid results only in case of missingness-at-random, multiple imputation approaches are taken to assess the robustness of the results. Specifically, missing values due to death, illness or chance are separately imputed assuming mixtures of missingness-not-at-random patterns. Imputation data sets are post-processed by multiplication with factors and addition of offsets (tipping point analysis). Proxy measures are taken into account to ameliorate the effects of attrition.

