| Statistical Analysis | 
Sample size: 300 (to be screened)
 
Trial population:
Full-analysis-set population (FAS, Intention-to-treat population): 248
 
Per-protocol-set population (PPS):
198
(defined as a subset of the FAS population patients without major protocol violations.)
 
Efficacy / test accuracy: The evaluation is based on change on the GDS with a range of 0-30 points.
 
Description of the primary efficacy analysis and population: The primary (full) analysis set (FAS) is derived from the intention-to-treat principle (all subjects randomized with a valid baseline assessment and at least one valid follow-up outcome assessment). The change in GDS from baseline to end-of-treatment is evaluated by means of a mixed model for repeated measures (MMRM) with fixed effects group, time, group*time, therapist and baseline value; corresponding treatment contrasts are based on marginal means. To assess the impact of up to 20% attrition multiple imputation approaches are taken, accounting for proxy measures and assuming specific missingness-not-at-random patterns. The details are documented in a statistical analysis plan. Analysis of subjects essentially observed and treated per protocol (PP) is supportive. Subgroup analysis is done i.a. by gender and disease severity (moderate, severe).
 
Safety: Adverse events are listed and summarized by group and category, seriousness, severity, relatedness, respectively.
 
Secondary endpoints: Quantitative outcomes are summarized by mean, standard deviation and percentiles (i.e. 0, 25, 50, 75, 100), qualitative outcomes by count (percentage). Differences between treatment groups and changes over time are essentially evaluated along the same line as for the primary outcome measure, i.e. using mixed modeling (or GEEs).
 |

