##### **Primary Endpoint**

The primary outcome measure „change in GDS from baseline to end-of-treatment“ is evaluated by a mixed model for repeated measures (MMRM) with fixed effects baseline, therapist, group, time and the interaction group\*time (ARH1-structured covariance matrix over time) with corresponding marginal means and contrast tests. Data from low recruiting therapists (i.e. <4 subjects) are pooled by study centre. The potential clustering of observations of participants by therapist or centre will be investigated by multilevel modelling [5]. Since mixed models can be expected to yield valid results only in case of missingness-at-random, multiple imputation approaches are taken to assess the robustness of the results. Specifically, missing values due to death, illness or chance are separately imputed assuming mixtures of missingness-not-at-random patterns. Imputation data sets are post-processed by multiplication with factors and addition of offsets (tipping point analysis) [8]. Proxy measures are taken into account to ameliorate the effects of attrition.

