### 2.1.4 Blinding

This is a single-blind (observer-blinded) trial. The primary and secondary outcomes will be obtained at baseline, in week 5 after 7 treatment sessions, in week 10 at the end of treatment and at follow-up (6 months after randomization) by the rater, who will be blinded to the treatment arm allocation.

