### 2.6.4 Secondary analyses

The secondary objective of this study is to test the efficacy of LLD-CBT in comparison with SUI on patient reported outcome in major depressive disorder, anxiety, sleep, cognition, quality of life and overall health status. Furthermore, we will be investigating the influence of childhood traumatic experiences and personality traits on the change of depressive symptoms in LLDCBT in comparison to SUI.

Secondary outcomes (i.e. further time points and measures) are analyzed along the same lines, i.e. using mixed modeling (or GEEs). Time-to-event (e.g. drop-out or survival) distributions are summarized by the

Kaplan-Meier method and compared by the (stratified) log-rank test. Analysis of the set of subjects essentially observed and treated per protocol (PP) is supportive; similarly the compliers' average causal effect (CACE) is calculated [11]. Subgroup analyses are done by study site and gender (expected male to female ratio 1:2); interaction with treatment is investigated. Quantitative outcomes are summarized by mean, standard deviation and percentiles (i.e. 0, 25, 50, 75, 100), qualitative outcomes by count (percentage).

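### The primary MMRM gives baseline GDS one slope for all visits; a baseline-by-time term is a low-cost safeguard, mainly for the month-6 contrast, if slopes change over time and drop-out depends on baseline differently by arm

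*Combined protocol and SAP*

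**What the plan says.** The primary model is stated three times, each time with baseline as a single main effect and group-by-time as the only interaction.

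- Synopsis (1.1), Statistical Analysis: "with fixed effects group, time, group*time, therapist and baseline value".
- Protocol 1.14.3, Primary Endpoint: "mixed model for repeated measures (MMRM) with fixed effects baseline, therapist, group, time and the interaction group\*time".
- SAP 2.6.3: "with fixed effects baseline, therapist, group, time and the interaction" of group with time, under an ARH1 covariance.

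GDS is taken at baseline and then "in week 5 after 7 treatment sessions, in week 10 at the end of treatment and at follow-up (6 months after randomization") (SAP 2.1.4). The primary variable is "Change in Geriatric Depression Scale (GDS) from baseline to end-of-treatment (week 10") (SAP 2.4.2). SAP 2.6.4 adds: "Secondary outcomes (i.e. further time points and measures) are analyzed along the same lines". The text does not list the visits that enter the primary fit. That month 6 shares it is inferred from the word time and from this sentence.

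SAP 2.6.3 accepts that the mixed model needs missingness at random, and adds multiple imputation with tipping-point offsets as a robustness check. No supplementary or sensitivity analysis is said to include baseline by time.

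**The concern.** A common slope is harmless while the arms have the same mean baseline among those observed. If drop-out removes patients of different baseline severity from the two arms, the arms differ in baseline at T2 and T3, and the model corrects that gap with the common slope. If the slope at that visit is different, part of the gap stays in the treatment contrast.

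Drop-out that depends only on arm and baseline is missing at random, which is the case the plan relies on its MMRM to handle. The fault would lie in the mean model, so neither another covariance structure nor a not-at-random sensitivity analysis corrects the primary estimate. Analysing change instead of the score does not help either, since it lowers every visit's slope by one and leaves their differences as they were.

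At stake are the week-10 contrast and, more so, GDS at month 6, the first-named key secondary endpoint (1.8.2.2).

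**Working it through.** **1. The plan's own figures.** Sample size: 2 × (1.96 + 0.8416)² / 0.4² = 98.1, so 99 per group; 99 / 0.8 = 123.75, so 124. The stated numbers reproduce, and the point does not touch them.

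**2. The slope implied at month 6.** Slope = correlation × later SD / baseline SD. With the assumed correlation of 0.5 and the pilot SDs (1.14.1, SAP 2.1.7):
- CBT arm: 0.5 × 6.42 / 3.92 = 0.82.
- Control arm: 0.5 × 7.58 / 3.96 = 0.96.
- Rounded average: 0.5 × 7.0 / 3.94 = 0.89.

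No correlation is given for week 5 or week 10, so the earlier slopes must be assumed.

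**3. Why both conditions are needed.** To first order, the shift at visit t is (common slope − true slope at t) × (baseline gap between arms among those observed at t). It vanishes if either factor is zero. Simulation with 124 per arm and about 20% drop-out agrees:
- Equal slopes (0.9 at each visit), drop-out opposite by arm: 0.00 at T2, 0.01 at T3.
- Slopes 0.98/0.89/0.71, drop-out unrelated to baseline: 0.00 at both.
- Slopes 1.0/0.8/0.5, drop-out related to baseline in the same way in both arms: 0.00 at T2, within 0.015 at T3.

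**4. Size when the month-6 slope is about 0.89.** Entries are the difference between the common-slope and baseline-by-time contrasts, in GDS points. Drop-out occurs after T1.

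| Assumed slopes T1/T2/T3 | Drop-out log-odds per baseline point | T2 | T3 |
|---|---|---|---|
| 1.0/0.95/0.89 | 0.10 in one arm only, or ±0.08 to ±0.15 opposite by arm | 0.02–0.04 | 0.03–0.10 |
| 1.08/1.0/0.89 | as above | 0.02–0.05 | 0.04–0.15 |
| 1.01/0.99/0.89 | ±0.10 to ±0.15 opposite by arm | about 0.01 | 0.07–0.12 |
| 1.21/1.06/0.89 | as above | 0.09–0.13 | 0.18–0.28 |
| 1.41/1.12/0.89 | as above | 0.17–0.25 | 0.30–0.45 |

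The first two rows use residual SDs 5.5/6.1/6.3 and a known covariance (400 replicates). The last three extend the ARH1 decay back to baseline, with correlation 0.5 at month 6 and GDS SDs of 5/6.2/7, 6/6.6/7 and 7/7/7 (300 replicates).

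Against the target, 0.1 / 2.5 = 4% and 0.25 / 2.5 = 10%.

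**5. What larger values require.** These runs used REML with ARH1, residual SDs 5.0/6.1/6.3, and drop-out log-odds of ±1 per baseline SD, opposite by arm (1 / 3.94 = 0.25 per point, stronger than in step 4). The baseline gap among those observed at T2 was about 1.4 points. The implied month-6 correlation is slope × 3.94 / √(6.3² + (slope × 3.94)²).

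| Slopes | Month-6 correlation | T2 | T3 |
|---|---|---|---|
| 0.98/0.89/0.71 | 0.41 | 0.08 | 0.38 |
| 1.0/0.8/0.5 | 0.30 | 0.19 | 0.70 |
| 1.0/0.6/0.3 | 0.18 | 0.44 | 0.94 |

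In the first two rows, type I error of the common-slope test was 0.049 and 0.054 at T2, and 0.055 and 0.106 at T3 (800 replicates).

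**6. Cost of the extra term.** Under the opposite drop-out of step 5, the model SE at T2 went from 0.847 to 0.856 (about 1%), and at T3 it rose by 0 to 2%. With drop-out unrelated to baseline, T2 was 0.843 against 0.844. The bias with the term was within simulation error. Therapist effects were not simulated.

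**The case against.** The strongest case against is that neither condition is documented. Nothing in the protocol says that the influence of baseline fades, or that severe patients will leave one arm and mild patients the other. Both arms have the same number of sessions, the same therapists and a manual. Opposite-sign drop-out is a harsh scenario, and the one-arm version gives smaller shifts. This stands, and it limits the point to a safeguard.

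It does not remove the point. Under the plan's own ARH1 pattern, extended back to baseline with correlation 0.5 at month 6, a constant slope would need the GDS SD to grow by 1 / 0.5^(1/3) = 1.26 at every visit, which nothing supports. Section 1.10.4.3 ends participation for worsening depression that needs inpatient care or a medication change, and for acute suicidality. Those exits are linked to severity and could differ by arm if the treatments differ. The attempt in 1.10.4.2 to assess patients after drop-out would reduce the loss.

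The planned multiple imputation is a partial answer. Completed data sets close the baseline gap, provided that the imputation model lets baseline act separately at each visit. The SAP does not specify that model, and it is a sensitivity analysis.

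A reader might go further and infer that the primary test is materially biased, or that arm-specific drop-out alone is enough to bias it. The documents support neither. With equal slopes the two models agree, and a low month-6 slope such as 0.4 or 0.54 implies a correlation of about 0.24 or 0.32 (residual SD 6.3), against the planned 0.5.

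**Conclusion.** The point holds as a modest one. The planned model imposes a single baseline slope, and this can mis-adjust the contrasts when changing slopes and arm-specific, baseline-related drop-out occur together. With month-6 slopes consistent with the plan, the shift is about 0.01 to 0.25 points at T2, under 0.1 in most runs, and about 0.03 to 0.45 at T3. The direction depends on which arm loses its more severe patients.

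These sizes rest on assumed slopes at weeks 5 and 10, assumed drop-out odds, and month 6 being in the same fit. If month 6 is fitted separately, the T3 figures do not apply in this form; that case was not simulated. The change is worth making because it costs almost nothing, but the validity of the primary test has not been shown to depend on it.

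**What to change.** In the synopsis, protocol 1.14.3 and SAP 2.6.3, list the fixed effects as baseline GDS, baseline GDS by time, therapist, group, time, and group by time. State which visits the model includes. For secondary scales with several post-baseline visits (QIDS-C and GAI, for example), use each scale's own baseline by time. Measures taken after baseline only at month 6, such as CERADplus and the NAB subtest in the protocol 1.11.2 schedule, do not need it.

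The cost is a wording change, two parameters per model with three visits, and about 0 to 2% in standard error. No new data are needed, and the sample size stays at 124 per arm, 248 in total.

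### The primary MMRM's ARH(1) covariance forces equal adjacent-visit correlations across gaps of 5 and about 16 weeks; an unstructured matrix removes a small, conditional risk of bias at no measurable cost

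*Combined protocol and SAP*

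**What the plan says.** The primary variable is "Change in Geriatric Depression Scale (GDS) from baseline to end-of-treatment (week 10") (SAP 2.4.2). SAP 2.6.3 analyses it by an MMRM with "fixed effects baseline, therapist, group, time and the interaction group" by time, and with an "ARH1-structured covariance matrix over time) with corresponding marginal means and contrast tests". Protocol 1.14.3, Primary Endpoint, names the same "ARH1-structured covariance matrix over time".

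Post-baseline outcomes are taken "in week 5 after 7 treatment sessions, in week 10 at the end of treatment and at follow-up (6 months after randomization") (SAP 2.1.4). With baseline as a covariate, the repeated measures are therefore T1, T2 and T3.

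Neither document gives a reason for ARH(1), an alternative structure, a robust standard error or a sensitivity analysis on the covariance. The robustness work that is planned concerns therapist pooling, clustering by therapist or centre, and missingness not at random (multiple imputation with tipping point).

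**The concern.** ARH(1) lets each visit have its own variance but allows only one correlation parameter, ρ: corr(T1,T2) = corr(T2,T3) = ρ and corr(T1,T3) = ρ². It treats a 5-week gap inside the treatment phase and a gap of about 16 weeks, mostly after treatment, as the same step.

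With complete data this hardly touches the T2 contrast. With dropout, the covariance supplies the implicit prediction of a missing T2 value from the observed T1 value. The SAP relies on the mixed model being valid under missingness at random; for a likelihood model that also requires an adequate covariance. If ρ is a compromise between two different correlations, T2 is mispredicted for patients who leave. If those patients differ between arms, the error does not cancel.

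Outcome-related loss is conceivable here. Protocol 1.10.3 and 1.10.4.3 link discontinuation to a change of antidepressive medication and to worsening depression, and assessment after drop-out is to be made only where feasible (1.10.4.2). In the pilot the control arm improved less (20.68 to 14.92, against 19.26 to 10.67), so such events could be more frequent in one arm.

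**Working it through.** **The plan's own figure.** SAP 2.1.7 targets a "clinically relevant difference of 2.5 GDS points" with d = 0.4, 80% power and two-sided 5%. n = 2(1.960 + 0.842)²/0.4² = 98.1, so 99 per arm; 99/0.8 = 123.75, so 124 per arm and 248 in total. This reproduces. It rests on a t-test and does not depend on the covariance structure.

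**Inputs from the documents.** T1 at week 5, T2 at week 10, T3 at 6 months (about week 26): gaps of 10 − 5 = 5 and 26 − 10 = 16 weeks. 124 per arm, up to 20% attrition. Covariance parameters: ARH(1) 3 variances + 1 correlation = 4; unstructured 3 + 3 = 6.

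**Assumptions, not in the documents.** Residual SDs 5.5, 6.1 and 6.1; the three between-visit correlations; dropout logistic in the last observed residual (a log-odds slope of 1 per SD at T1 reproduces the table below).

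**Mechanism.** If all loss occurs after T1, the fitted T2 mean in arm g is

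mean T2 of completers + b × (mean T1 of all − mean T1 of completers),

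where b is the model's slope of T2 on T1. The bracket equals p_g × (mean T1 of dropouts − mean T1 of completers) = Δ_g, with p_g the dropout proportion. So

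error in the contrast = (b under ARH(1) − true b) × (Δ_CBT − Δ_SUI).

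It is zero if either factor is zero. To illustrate the first factor: if correlation decays with time and is 0.70 over 5 weeks, it is 0.70^(16/5) = 0.32 over 16 weeks. The true slope is 0.70 × 6.1/5.5 = 0.78; at a common ρ midway between (0.51) it would be 0.51 × 6.1/5.5 = 0.57.

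**Large-sample likelihood fits.** Difference in the T2 contrast, ARH(1) minus unstructured, in GDS points, all loss after T1 (correlations T1–T2 / T2–T3 / T1–T3):

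| Dropout | .75/.55/.50 | .70/.40/.30 | .70/.32/.22 |
|---|---|---|---|
| Same mechanism, 20% in each arm | 0.00 | 0.00 | 0.00 |
| Same mechanism, 15% v 25% | 0.04 | 0.06 | 0.08 |
| Same direction, slope doubled in one arm | 0.04 | 0.06 | 0.08 |
| Outcome-related in one arm only, 20% each | 0.08 | 0.13 | 0.17 |
| Opposite directions, 20% each | 0.17 | 0.27 | 0.35 |

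Against 2.5 points: 0.04/2.5 = 1.6%, 0.17/2.5 = 6.8%, 0.35/2.5 = 14%. Outcome-related loss in one arm only, combined with rates of 15% v 25%, gives about 0.10 to 0.21.

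In these sets the shift dilutes a benefit of CBT if the patients doing worse leave SUI; the formula reverses the sign if they leave CBT.

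**Sensitivity to the assumptions.** For opposed dropout with correlations .65/.65/.50 the shift is 0.003; with .60/.70/.50 it is −0.085. For .70/.32/.22, splitting the loss as 10% after T1 and 10% after T2 lowers the opposed shift to 0.16.

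**Cost of the unstructured matrix, 248 patients, 1,500 simulated trials.** When ARH(1) is true (.6/.6/.36) and dropout is the same in both arms, the SE is 0.802 and power 85.9% under both structures. In a separate check with therapist fixed effects included (28 therapists assumed), the empirical SD of the contrast was 0.86 under both. With .70/.32/.22 and opposed dropout (10% + 10%), power was 82.1% under ARH(1) and 86.8% unstructured.

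**The case against.** The tempting stronger reading is that ARH(1) biases the primary result whenever patients drop out. The documents do not support it. Both arms receive the same number and frequency of sessions from the same therapists (protocol 1.9.2, 1.11.3.3), and nothing in the documents suggests opposed dropout. With the same mechanism and rate in both arms the two models agree.

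Nor do the documents show that the 16-week correlation must be the lower one. T1–T2 lies within active treatment, when patients change at different speeds; T2–T3 is mostly after it. Correlation need not fall with calendar time across that boundary. The only correlation given is 0.5 between baseline and follow-up. This stands: inequality is likely enough to allow for, but it is not established.

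The exposed fraction may also be smaller than 20%. That figure is an upper bound, and the pilot lost 11%. A drop-out is defined chiefly as stopping before session 9, and T1 follows session 7, so some loss may precede T1. Such patients, if never assessed again, are outside the full analysis set and the covariance cannot affect them. With half the loss before T1, even the opposed shift falls to 0.09 to 0.20.

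A reader might also infer type I error inflation from 5.5% against 4.7% in the opposed time-decay case. At 1,500 runs the Monte Carlo standard error is √(0.05 × 0.95/1500) = 0.6 percentage points, so this is not shown. Power in that case still exceeded the planned 80%.

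Finally, imputation and tipping-point analyses do probe conclusions against mispredicted dropouts. But they target departures from missingness at random. If they disagreed with the MMRM, a covariance artefact could not be told apart from informative missingness.

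**Conclusion.** The point holds as a prespecification weakness of modest expected impact. Bias needs two conditions together: unequal adjacent correlations, and outcome-related dropout that differs between arms in mechanism or rate. Under both, the T2 contrast moves by about 0.04 to 0.17 GDS points for moderate arm differences and by up to about 0.35 in the extreme case. Otherwise it is zero. Even 0.35 is less than half a standard error (0.35/0.80 = 0.44). All sizes rest on assumed correlations, SDs and dropout mechanisms.

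The case for changing is that the restriction buys nothing: at 248 patients, two further covariance parameters had no measurable effect on precision. The change guards only against covariance misspecification under missingness at random, and the sample size is unaffected.

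**What to change.** In protocol 1.14.3 and SAP 2.6.3, replace ARH(1) by an unstructured 3×3 covariance over T1, T2 and T3. State an ordered fallback for non-convergence only: heterogeneous Toeplitz, then ARH(1). Report which structure was used. Heterogeneous Toeplitz frees the T1–T3 correlation but still holds the two adjacent ones equal, so it helps with convergence and gives no protection on this point.

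The cost is one line of text and code, and two more parameters. SAP 2.6.4 analyses secondary outcomes along the same lines, so the edit carries over to those measured at all three visits. Leave the imputation and tipping-point analyses as planned, since they cover missingness not at random. A baseline-by-time term and the degrees-of-freedom method are separate questions not examined here.
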